**Acceptability**
I like this app
I want to keep using this app
This app helps me to eat healthy
I like receiving badges
I like the daily diet reports
I like the daily statistics page
I like the weekly statistics page
I like following other users
I like to be part of a team
I like the general navigation of the screens
**Usability**
This app is simple to understand
I felt comfortable using this app
I felt praised when I ate healthy foods
I felt supported by my app friends
I can take pictures of my meals at home
I can take pictures of my meals in school
I can take pictures of my meals when I am eating with my family
I can separate what I eat from what others are eating to take pictures
I trust this app's feedback about my diet
I trust this app's information about healthy eating

Responses are in Likert scale from 1 = strongly agree to 5 = strongly disagree.

Based on the analysis of the program theory, the effects of the FRANI and gamified nudges on the dietary quality of adolescent girls will be assessed on a set of secondary outcomes including the percentage of meals recorded and the quality of food choices. The quality of food choices will be measured according to the Dietary Diversity Score (DDS) and the Sustainable Healthy Diet Score (SHDS). Adherence, percentage of meals recorded, the DDS and the SHDS will be measured using data captured by FRANI. Although the secondary outcome measures will be based on intervention and control group comparisons, the primary measures will not.

The data for outcomes will be recorded on FRANI and uploaded to a data collection platform at real time during the intervention period. Data collection will happen automatically once the participants took pictures of the foods they ate and confirmed their recognition. Since the image recognition technology from FRANI has been shown to be promising in the validation study (not published yet), the automatization of the data entry process may minimize mistakes if compared to other forms of food consumption data collection such as 24 h recalls and food frequency questionnaires. Baseline variables such as parents occupation, household assets and school performance will be collected with questionnaires. The data will be stored in protected clouds at the Pennsylvania State University.

### Sample size

The sample size was determined by the number of smartphones and data packages that could be supported by budget and is consistent with other pilot studies in the literature. The effect size of the treatment on the DDS and the SHDS on the first four weeks of the study will be used to calculate the sample size of a larger experiment.

### Statistical analysis

The data from the pilot studies from Ghana and Vietnam will be analyzed and reported separately, though a pooled analysis will also be undertaken once both pilots have been completed. The analysis will be by intent to treat, and we do not expect to have loss of follow-up as this is a small scale pilot. Descriptive statistics and balance tables will be calculated for all variables and will be presented as medians or means with standard deviations. Differences in the outcomes between intervention and control groups will be estimated by multi-level Poisson regression models with the DDS and the SHDS as outcomes, a dummy variable for the treatment, a continuous time variable for the days and an interaction of treatment and time, and random effects at the individual level to account for the repeated measures. We will also undertake exploratory analysis for each food group of the DDS and the SHDS separately using odds ratio regressions. Socio-demographic variables that were not balanced after randomization will also be included in the robustness analysis.

A *p*-value < 0.05 will be considered statistically significant and *p*-value < 0.1 will be considered marginally significant. We will assess the need to screen outliers values greater than three standard deviations and will analyze the sensitivity of the treatment effect to the outliers.

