The options for setting food consumption goals were based on the EAT-Lancet Diet (23) and the Dietary Guidelines of Vietnam (24). These FRANI goals can be individual- or team-oriented, and involve five main food groups: (1) grains and starchy staples; (2) legumes, nuts and seeds; (3) fruits and vegetables; (4) dairies; (5) animal-source foods (excluding dairy). In addition to setting food consumption goals, participants from the intervention group be nudged with game elements. These nudges include: (1) tracking progress towards healthy-eating goals; (2) giving personalized feedback on food consumption; (3) reinforcing healthy food consumption; (4) tracking progress in the quality of food consumption with statistics; (5) participating in goals shared with other users (team-based goals); (6) sharing positive feedback with peers. Participants in the intervention group will be able to choose from team-based goals on a weekly basis. They will receive information about their team's overall performance but in order to avoid excessive peer pressure they will not be able to see each individual team member's performance.

The study protocol and the methods and materials were approved by the Institutional Review Board (IRB) of the IFPRI on April 29th, 2020 (registration number #00007490), the Thai Nguyen National Hospital on April 14th, 2020 (protocol code 274/ĐĐĐ-BVTWTN) and the University of Ghana on August 10th, 2020 (Federalwide Assurance FWA 00001824; NMIMR-IRB CPN 078–19/20). The study protocol was registered in the International Standard Randomized Controlled Trial Number (ISRCTN 10681553; https://doi.org/10.1186/ISRCTN10681553) on November 12, 2021. Participants will be instructed to report any problem occurring during the study to the country-lead researchers, which will be in direct contact with them. Although risk from using FRANI is minimal, any adverse effect will be discussed by the team, and reported to the IRB of the IFPRI and to the ethics boards of correspondent countries. All procedures were and will be in accordance with the Declaration of Helsinki.

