### Inclusion and exclusion criteria, and recruitment

A total of 72 adolescents girls aged between 12 and 18 years will be randomly selected from two schools, one in each city, which staff has a good working relationship with our team. Those who assented for participation and which parents consented will receive a smartphone pre-configured with the FRANI app. Participants will be free to discontinue study participation at any time. Candidates will be excluded from the study if they do not provide assent or their parents do not provide consent to participate.

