### Randomization and allocation

A computer-generated random number will randomize participants in the intervention and control groups at a 1:1 ratio for each country separately. The allocation sequence will be generated and the enrollment and assignment will be done by the senior researchers of the Vietnamese and Ghanaian teams. Although a similar description of FRANI will be presented for intervention and control groups in the process of informed assent and consent, it will not be possible to blind who is receiving feedback from FRANI and who is not. The data will be collected by the application without assessors.

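### The only model described omits country, the randomisation stratum; if used for the pooled analysis it would overstate the standard error of the arm level contrast

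*Protocol article*

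**What the plan says.** All statements are in the protocol article.

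- **Randomization and allocation:** the section states: "A computer-generated random number will randomize participants in the intervention and control groups at a 1:1 ratio for each country separately". Country is therefore a randomisation stratum.
- **Inclusion and exclusion criteria, and recruitment:** on the source of the sample, the section states: "A total of 72 adolescents girls aged between 12 and 18 years will be randomly selected from two schools, one in each city". Country and school coincide, so one term covers both.
- **Statistical analysis, data sets:** each country is analysed and reported on its own, "though a pooled analysis will also be undertaken once both pilots have been completed".
- **Statistical analysis, model:** arm differences "will be estimated by multi-level Poisson regression models with the DDS and the SHDS as outcomes". The fixed effects are "a dummy variable for the treatment, a continuous time variable for the days and an interaction of treatment and time", with "random effects at the individual level to account for the repeated measures". No separate model is given for the pooled fit.
- **Statistical analysis, covariates:** socio-demographic variables found unbalanced after randomisation enter a robustness analysis. No other adjustment rule is given.
- **Outcomes:** DDS and SHDS are secondary and compared between arms over the first four weeks. The primary feasibility outcomes are not arm comparisons.
- **Sample size:** the number of girls was set by budget, without a power calculation. The DDS and SHDS effects will inform the size of a larger experiment.

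**The concern.** The listed terms suit an analysis of one country. Carried over unchanged to 72 girls from two countries, they leave out the factor within which allocation was balanced. Girls in Accra and Thai Nguyen may well differ in mean daily score. Without a country term, the model can only read that difference as variation between individuals, so the random-intercept variance grows.

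With equal arms inside each country, however, the country difference cancels out of the arm comparison. The estimate does not vary as much as the model believes. The consequence is a standard error that is too large for contrasts in level, a real type I error below the nominal 5%, and lost power. With about 18 girls per arm per country, the pooled fit is the most precise arm comparison the study offers, so the loss falls where precision is most needed.

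**Working it through.** The plan states no effect size, SD or power, so there is no figure to reproduce. The check covers the mechanism and its plausible size.

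**Inputs from the article:** 72 girls, two countries, 1:1 within country (taken as 18 per arm per country), 28 daily scores, alpha 0.05 (two-sided assumed).

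**Assumptions not in the article:** mean daily score 4.5; person SD s of 0.10 to 0.30 on the log scale; ratio R of country means of 1.1 to 1.5; 28 complete days, coded 0 to 27; parallel day trends and the same treatment effect in both countries; Poisson variation within girl, as the model supposes.

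**Formulas (log scale):**

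- SE² of a level contrast = (4/72) × (s² + w), where w is the within-girl variance.
- Omitting country adds k = (ln R)²/4 to s², because half the girls lie ½ ln R above the middle and half lie ½ ln R below it.
- Four-week average: w = 1/(28 × 4.5) = 0.00794.
- Day-0 treatment coefficient: w₀ = (1/4.5) × (1/28 + 13.5²/1827) = 0.0301, where 1827 = 28 × (28² − 1)/12.
- Treatment-by-day: SE² = (4/72) × (1/4.5)/1827, so SE = 0.00260 per day. Neither s² nor k enters, so the inflation factor is 1.00.

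**Worked case, s = 0.15 and R = 1.3:** s² = 0.0225 and k = 0.2624²/4 = 0.0172.

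- Average contrast with country: √[(4/72) × 0.0304] = 0.0411. Without country: √[(4/72) × 0.0476] = 0.0514. Ratio 1.25.
- Day-0 coefficient: √[(0.0526 + 0.0172)/0.0526] = 1.15.
- Real alpha for the average contrast: the estimate must exceed 1.96 × 1.251 = 2.452 true standard errors, which gives 0.014.
- Power, for an effect with 80% power when country is included: Φ(2.802 − 2.452) = 64%.

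**Across the assumed range** (power and alpha refer to the average contrast without country):

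| Person SD | Country ratio | Average contrast, SE factor | Day-0 coefficient, SE factor | Power in place of 80% | Real alpha |
|---|---|---|---|---|---|
| 0.30 | 1.1 | 1.012 | 1.009 | 79% | 0.047 |
| 0.20 | 1.2 | 1.083 | 1.058 | 75% | 0.034 |
| 0.15 | 1.3 | 1.251 | 1.152 | 64% | 0.014 |
| 0.10 | 1.5 | 1.814 | 1.423 | 22.5% | 0.0004 |

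**Check by simulation.** The random-intercept Poisson model with the listed terms was fitted to 150 simulated data sets with s = 0.15, R = 1.3 and a constant log effect of 0.12. With 150 runs, a rate near 62% has a Monte Carlo error of √(0.62 × 0.38/150), or about 4 points.

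| Quantity | Without country | With country |
|---|---|---|
| Average contrast, reported SE | 0.0506 | 0.0396 |
| Average contrast, actual SD of estimates | 0.0390 | 0.0380 |
| Average contrast, power | 62% | 84% |
| Day-0 coefficient, reported SE | 0.0609 | 0.0521 |
| Day-0 coefficient, rejection rate | 45% | 57% |
| Treatment-by-day, reported SE (over the 28 days) | 0.0676 | 0.0676 |

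The estimate scatters about equally in both fits. Only its reported error is too wide without country. In a second run the effect grew from zero to 0.12 by the last day. The treatment-by-day term detected it in 37% of data sets with either model.

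**The case against.** **No pooled model is actually stated.** The listed terms are right for the single-country analyses, where a country term cannot be fitted. The article is condensed, and a statistical analysis plan that is not shown may add country. This stands to the extent that the point must be conditional on the listed model being used for the pooled fit. It does not remove the point. The section commits to pooling, lists its terms explicitly, and gives an adjustment rule that would not select a factor balanced by design. Followed literally, it produces worse error bars than the design allows.

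**A reader might infer that the omission can hide any treatment effect.** The documents do not support that. The same model contains treatment-by-day, a within-girl contrast that a country difference in level does not touch. Only contrasts in level are affected. The largest inflation also belongs to the four-week average, a contrast the section does not name; the treatment coefficient itself refers to day 0 and is inflated less.

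**A reader might infer that pooling conceals different effects in Ghana and Vietnam.** It does not, because each country is also to be reported separately.

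**Little depends on it.** DDS and SHDS are secondary, no power is claimed, and the point estimate is essentially as precise either way. This stands and keeps the point modest. The effect estimates are nevertheless meant to inform a larger trial, so their stated uncertainty should be right.

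**Conclusion.** The point holds in a limited form. If the listed model is used for the pooled analysis, the reported standard error of the treatment coefficient and of the average arm contrast is too wide whenever mean scores differ between countries. The test is then conservative. It introduces neither bias nor extra false positives, and it leaves treatment-by-day, the separate country analyses and the primary outcomes alone.

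The size cannot be fixed from the documents. It runs from negligible (about 1%) to large (81% for the average contrast, 42% for the day-0 coefficient) over the assumed person SDs and country ratios. The conservatism rests on equal arms within each country. The factor of 1.00 for treatment-by-day rests on parallel day trends. This is a free improvement to a secondary analysis, not a flaw that threatens the pilot's main conclusions.

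**What to change.** In Statistical analysis, add one sentence: the pooled Poisson models for DDS and SHDS include country, the randomisation stratum, as a fixed effect in addition to the listed terms. Because there is one school per country, this also covers school.

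A country-by-day term (if time trends may differ) and a treatment-by-country estimate with its confidence interval are optional. The separate country reports stay as planned. If the statistical analysis plan already includes country, the article need only say so.

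The required change costs one sentence and one model parameter per outcome, with no new data and no change to conduct.

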**Figure 2 F2:**
[figure not shown]
The stylized program impact pathways for the FRANI. (Source: Adapted from (21)) Notes: Yellow represents the two steps users have to follow to have their dietary consumption tracked and to be nudged to make healthier food choices. Green boxes show nudges to influence the use of the FRANI and healthy food choices. Blue boxes represent what is expected to improve with the FRANI use. Gray is for a possible unintended consequence of the FRANI use that should be fixed in future versions of the app.

The main differences in the application versions for the intervention and control groups are described in Table 1. Briefly, both the intervention and control versions of FRANI recognize food images, assess the quality of the user's diet, and receive notifications with reminders to take pictures. However, only the treatment group can set food consumption goals, see the home screen, scores and statistics about dietary quality, receive badges and receive a daily report summarizing everything they ate in that day.

**Table 1 T1:** Features of FRANI by intervention group in the first four weeks of the pilot study.

Feature	Intervention	Control
Meal entry (picture taking)	X	X
Recognize food image in pictures	X	X
Assess quality of user's diet	X	X
Notifications	X	X
Setting goals	X	NA
Home screen	X	NA
Scores and statistics	X	NA
Medals and badges	X	NA
Daily report	X	NA
Activity feed	X	Modified
Daily report	X	NA

NA, not available. At the end of the fourth week, the control group switches to the intervention version and all participants use the same version of FRANI for two weeks to measure adherence, acceptability and usability.

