### Outcomes

The feasibility of FRANI will be assessed by measuring outcomes related to adherence, acceptability, and usability as summarized in Table 2 (25, 26). According to the World Health Organization (WHO), adherence is “the extent to which a person's behavior – taking medication, following a diet, or executing lifestyle changes, corresponds with agreed recommendations from a health care provider” (27). Although there is no consensus in the literature on the best measure for adherence to eHealth technology interventions (25, 26), maximum benefit from the intervention as defined by creators should be considered (28). We define the sample adherent to FRANI if 70% or more of participants-days upload complete dietary recalls in the last two weeks of the pilot study. Acceptability summarizes likeability and satisfaction with FRANI, while usability summarizes what affects the use of the FRANI. Acceptability and usability are measured according to answers from structured questionnaires described in Table 3. If participants grade the acceptability or usability of FRANI as 30 or less points in their respective structured questionnaires, the app will be considered accepted or usable.

**Table 2 T2:** Domains and outcome measures for the FRANI pilot test.

Outcomes	Definition
Primary outcomes (feasibility)	
Adherence	The number of days participants upload completed dietary recalls on the FRANI divided by the total number of dietary recalls (complete + incomplete) of the last two weeks of the pilot test is equal to or higher than 70%
Acceptability	Summarizes likeability and satisfaction with FRANI according to answers from a structured questionnaire. If participants grade the acceptability of FRANI as 30 or less points on a scale from 10 to 50 points, the app will be considered accepted.
Usability	Summarizes possibility to use and intent to keep using FRANI according to answers from a structured questionnaire. If participants grade the usability of FRANI as 30 or less on a scale from 10 to 50 points, the app will be considered usable.
Secondary outcomes	
Percentage of meals recorded	The number of meals recorded on the FRANI divided by the number of total meals participants had during the last two weeks of the pilot test period.
Dietary Diversity Score^a^	Ranges from 0 to 10 points using MDDW dietary diversity food groups (daily score) measured in the first four weeks of the pilot study period.

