Sustainable Healthy Diet Score^b^	Ranges from 0 to 14 points using EAT-Lancet food groups (daily score) measured in the first four weeks of the pilot study period.

^a^
The dietary diversity score was calculated according to the Minimum Dietary Diversity for Women, A Guide for Measure (26).

^b^
The Sustainable Healthy Diet Score was calculated according to the study EAT- Lancet Score and Major Health Outcomes: The EPIC-Oxford Study (25).

**Table 3 T3:** Questionnaire about acceptability and usability of the FRANI application.

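### DDS is built only from photographed foods and the nudges also target app use, but recording is measured only in the last two weeks, so the stated plan cannot separate a recording effect from a diet effect in weeks 1-4

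*Protocol article*

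**What the plan says.** **How diet is measured.** Outcomes (text after Table 3): "Adherence, percentage of meals recorded, the DDS and the SHDS will be measured using data captured by FRANI". The same section adds: "Data collection will happen automatically once the participants took pictures of the foods they ate and confirmed their recognition". No independent dietary measure is described for the arm comparison.

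**When diet is compared.** Table 2 defines DDS as "Ranges from 0 to 10 points using MDDW dietary diversity food groups (daily score) measured in the first four weeks of the pilot study period" and SHDS as "Ranges from 0 to 14 points using EAT-Lancet food groups (daily score) measured in the first four weeks of the pilot study period".

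**What the intervention targets.** The Figure 2 notes say: "Green boxes show nudges to influence the use of the FRANI and healthy food choices". In weeks 1-4, "only the treatment group can set food consumption goals, see the home screen, scores and statistics about dietary quality, receive badges" and a daily report. Picture reminders go to both arms (Table 1).

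**When recording is measured.** Adherence is judged at the end: "We define the sample adherent to FRANI if 70% or more of participants-days upload complete dietary recalls in the last two weeks". Table 2 gives the percentage of meals recorded the same late window. By then the controls have switched to the full version (Table 1 footnote).

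**How diet is analysed.** Statistical analysis specifies a Poisson model with treatment, day, their interaction and a random person effect. The robustness checks named are unbalanced socio-demographic variables and outliers. The nearest remark on missing data is "we do not expect to have loss of follow-up as this is a small scale pilot". Under Sample size, the DDS and SHDS effects are to size the larger trial.

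**The concern.** DDS counts food groups. A meal that is eaten but not photographed can only lower that day's score or leave it unchanged, so measured DDS mixes diet with recording completeness. If goals, scores and badges make the intervention arm photograph more of the same meals, its DDS rises without any dietary change.

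The plan does intend to compare recording between arms, since the percentage of meals recorded is a secondary outcome. But its window opens only after the arms have stopped differing in app version. A recording gap during weeks 1-4, when diet is compared, would be neither reported nor adjusted for.

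At stake are the reading of the only between-arm diet result and the sample size of the next trial. A DDS effect inflated by recording would make that trial too small for the real dietary effect.

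**Working it through.** The article gives no power calculation, standard deviation or recording rate, so there is no figure to reproduce. The check asks how large a DDS difference arises when true diets are identical.

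**From the article:** 10 food groups; 36 girls per country at 1:1, so 36/2 = 18 per arm; 28 days; threshold p < 0.05.

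**Assumed:**
- Full-day probabilities of eating each group: 0.99, 0.35, 0.15, 0.25, 0.70, 0.45, 0.60, 0.40, 0.45, 0.50. They sum to a true mean DDS of 4.84.
- k = 3, 4 or 5 eating occasions a day, each recorded with probability r.
- SD of person means 0.7 to 1.0.

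**Formulas.** The per-occasion probability p_g solves 1 - (1 - p_g)^k = full-day probability of group g.
- Empty days scored 0: DDS(r) = sum over g of [1 - (1 - p_g r)^k].
- Empty days left out: DDS(r) / [1 - (1 - r)^k].

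**Example, k = 3, 85% v 70%.**
- Scored 0: 4.346 - 3.788 = 0.558.
- Left out: 4.346/(1 - 0.15^3) - 3.788/(1 - 0.30^3) = 4.361 - 3.893 = 0.468.

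**Standard error of the arm difference:** SD × sqrt(2/18) = 0.233 at SD 0.7 and 0.333 at SD 1.0.

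| Recording, intervention v control | False DDS difference, empty days scored 0 (k = 3-5) | Empty days left out | z over both treatments of empty days and SD 0.7-1.0 |
|---|---|---|---|
| 80% v 75% | 0.17-0.19 | 0.16-0.17 | 0.5-0.8 |
| 85% v 70% | 0.53-0.56 | 0.47-0.52 | 1.4-2.4 |
| 90% v 70% | 0.69-0.73 | 0.63-0.68 | 1.9-3.1 |

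**Second calculation with a different assumed diet.** Three meals a day; per-meal group probabilities 0.85, 0.25, 0.10, 0.10, 0.45, 0.15, 0.25, 0.12, 0.35, 0.12 (true DDS 5.28); person SD on the logit scale 0.25 for diet and 0.6 for recording; empty days left out. A t-test on 28-day person means at two-sided 0.05 stands in for the Poisson model.

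| Recording, control v intervention | Expected DDS | Ratio | False positives, 18 per arm | False positives, 36 per arm (pooled) |
|---|---|---|---|---|
| 70% v 70% | 4.31 v 4.31 | 1.00 | 5.5% | 4.4% |
| 70% v 75% | 4.31 v 4.47 | 1.04 | 10% | 14% |
| 70% v 80% | 4.31 v 4.63 | 1.07 | 24% | 45% |
| 70% v 90% | 4.31 v 4.96 | 1.15 | 78% | 96% |

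With equal recording the error rate is about nominal, so the excess comes from the recording gap. Pooling the countries makes a false finding more likely.

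**The case against.** **No recording gap is documented.** True. Bias needs a difference between arms, and the article gives none. Reminders reach both arms and local teams monitor all participants. These may narrow a gap but do not exclude one, and the article itself states that the nudges act on app use.

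**The 70% threshold.** A reader might infer that 30% of days in weeks 1-4 are expected to be incomplete. The threshold is a feasibility criterion for the last two weeks and says nothing about a gap between arms.

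**The no-loss sentence.** A reader might take it as the error. It concerns participants leaving, is not shown to be wrong, and can stay.

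**Which days are analysed.** It is tempting to say that all recorded days enter the model. The article does not say whether incomplete days enter or how empty days are scored, and an analysis plan could settle both. What stands is that the article itself places the recording outcomes in a window that cannot show the problem, beside a model without any recording term.

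**The test.** The z values and t-tests are stand-ins. In the planned model a constant gap would load mainly on the treatment term rather than the interaction, and the article does not say which term is the effect.

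**Conclusion.** The point holds as a structural weakness: photo-only measurement, nudges aimed at recording as well as diet, and recording outcomes defined only after the arms have converged. The stated plan therefore cannot tell a recording effect from a diet effect in weeks 1-4.

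For DDS the direction is clear: better recording in the intervention arm inflates the score. For SHDS bias is possible, but its sign is not determinable because the article does not give the scoring direction of the components.

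The size is conditional on the assumed diets, recording rates and SD. The false DDS difference runs from about 0.16 to 0.73 groups, and z from about 0.5 to 3.1. A reader might infer that a positive DDS result would be spurious, or that the artefact would be significant. Neither follows: a 5-point gap gives z below 1, and 85% v 70% passes 1.96 only towards the lower end of the assumed SD range.

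DDS and SHDS are secondary. The primary feasibility outcomes are not arm comparisons and are untouched. The change should be made, but it does not threaten the pilot's main purpose.

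**What to change.** 1. Report by arm, for days 1-28, the meals recorded per day and the share of days with a complete recall, in addition to the last-two-weeks measures.
2. State that a day with no upload is missing and is not scored 0.
3. Pre-specify a sensitivity analysis of DDS and SHDS limited to complete-recall days, or accounting for the number of meals recorded, and present it beside the main analysis.
4. Interpret a DDS or SHDS difference as a diet effect, or use it to size the larger trial, only in light of the recording comparison.

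**Cost.** Some wording and a small amount of extra analysis. Uploads are already captured by the app, and adherence already requires recalls to be classed as complete or incomplete. The article does not explain how that class is assigned, so the rule should be written down and applied to days 1-28 as well.

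**Downside.** The sensitivity analysis uses fewer days and conditions on a variable that arises after randomisation and may itself be affected by treatment. It supports the main analysis and does not replace it.

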## Methods and analysis

### Materials

The pilot studies are based on two-armed randomized controlled designs to be implemented in Ghana and Vietnam. In each country, 36 adolescents (12–18 years) will be randomly allocated into two groups: The intervention group with the full version of FRANI, including diet records and nudges to encourage healthier food choices. The control group will receive mobile phones with FRANI functionality limited to the dietary assessment. Participants in both groups will have their food choices tracked for a four week period. The control group will then switch to also use FRANI with full functionality and both groups will be tracked for a further 2 weeks to assess acceptability, adherence, and usability. The schedule of the intervention, enrollment and assessment is described in Figure 1. The stylized program impact pathway for the intervention is described in Figure 2 (21).

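### The Poisson mixed model for the bounded DDS and SHDS is likely to miscalibrate the treatment-by-time standard errors, in a direction the protocol does not settle

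*Protocol article*

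**What the plan says.** The Statistical analysis section of the protocol article states that differences between arms will be "estimated by multi-level Poisson regression models with the DDS and the SHDS as outcomes". The fixed terms are treatment, "a continuous time variable for the days and an interaction of treatment and time". The only other structure named is "random effects at the individual level to account for the repeated measures". No dispersion parameter, robust standard error or random slope for day is mentioned.

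Table 2 (Outcomes) gives the range of each score. The DDS entry reads "Ranges from 0 to 10 points using MDDW dietary diversity food groups (daily score" and the SHDS entry "Ranges from 0 to 14 points using EAT-Lancet food groups (daily score". The Statistical analysis section also plans to analyse each food group of both scores by odds ratios, which implies that each group contributes a yes/no point.

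On size and pooling, the Materials section says "In each country, 36 adolescents (12–18 years) will be randomly allocated into two groups", which gives 18 per arm. Allocation will "randomize participants in the intervention and control groups at a 1:1 ratio for each country separately". The countries are analysed separately, but "a pooled analysis will also be undertaken once both pilots have been completed". Country does not appear among the listed model terms.

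**The concern.** A Poisson model fixes the conditional variance at the mean. A random intercept or slope can only add variance to that. A score that counts yes/no items out of a fixed number usually varies less than this from day to day, and the stated model has no means of representing it. The standard error for treatment-by-time then comes out too large.

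A second error can act in the opposite direction. If girls differ in their true time trends and the model holds only a random intercept, those differences are missing from the standard error of the interaction.

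The planned 0.05 and 0.1 thresholds would be applied to these tests. With 18 girls per arm in each country, precision is scarce. The Sample size section says the DDS and SHDS effects will be used to size a larger trial, so a misstated variance could also be carried forward if it were taken from this model's output.

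**Working it through.** **No stated figure to reproduce.** The protocol gives no mean, standard deviation, effect size or power for either score; the sample size was set by budget. Only 2 × 36 = 72 can be checked, and it agrees. Every mean, variance and slope spread below is an assumption. Two-sided 5% is assumed.

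**Step 1: variance ratio.** For K independent yes/no items the variance is at most mean × (1 − mean/K). Write φ = true within-girl variance / mean; Poisson assumes φ = 1. With equal item probabilities, φ = 1 − mean/K. Unequal probabilities lower it further.

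**Step 2: effect on the test when all girls share one trend.**
- Standard error too large by 1/√φ.
- Type I error = 2 × (1 − Φ(1.96/√φ)).
- Power, if a correct standard error would give 80%: Φ(1.96 + 0.84 − 1.96/√φ).

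| Score | Mean | φ | SE ratio | Type I error | Power |
|---|---|---|---|---|---|
| DDS | 3 | 0.70 | 1.20 | 1.9% | 68% |
| DDS | 4 | 0.60 | 1.29 | 1.1% | 61% |
| DDS | 5 | 0.50 | 1.41 | 0.6% | 51% |
| DDS | 6 | 0.40 | 1.58 | 0.2% | 38% |
| SHDS | 6 | 0.57 | 1.32 | 1.0% | 58% |
| SHDS | 8 | 0.43 | 1.53 | 0.3% | 42% |
| SHDS | 10 | 0.29 | 1.87 | 0.02% | 19% |

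Example, DDS mean 5: 1.96/√0.5 = 2.77; 2.80 − 2.77 = 0.03; Φ(0.03) = 51%.

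**Step 3: simulation with a common trend.** 36 girls × 28 days, random-intercept Poisson fitted by maximum likelihood, 400 runs per scenario. Power is compared with a linear random-intercept model:
- DDS mean 4.5: 66% against 87%.
- SHDS mean 8: 48% against 85%.
- DDS mean 4.5 with unequal item probabilities (variance 1.8): 36% against 81%.

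**Step 4: simulation under no effect when girls' trends differ.** Slope SD is in logits per 10 days; figures are type I error.

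| Slope SD | Poisson, DDS 4.5 | Poisson, SHDS 8 | t-test on each girl's slope, DDS / SHDS |
|---|---|---|---|
| 0 | 1.8% | 0.0% | 6.8% / 4.0% |
| 0.1 | 2.8% | 1.5% | 4.5% / 4.3% |
| 0.2 | 12.8% | 8.3% | 6.5% / 4.5% |
| 0.3 | 25.0% | 21.0% | 6.2% / 3.3% |

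The Poisson test moves from conservative to liberal as trends diverge. With unequal DDS item probabilities and slope SD 0.2 the two errors nearly cancel (4.5%). A linear model with only a random intercept does no better: 23–38% at slope SD 0.2–0.3. A test that lets slopes vary by girl stays near 5%; the Monte Carlo standard error at 5% is √(0.05 × 0.95/400) = 1.1 points.

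**Step 5: four-week average.** In a further simulation (DDS mean 4.9, within-person variance 1.9), the ratio of model standard error to true SD for the average effect was 0.93–1.01.

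**Step 6: country in the pooled model.** Assume between-girl variance 0.5, daily variance 2 over 28 days, and a 1-point country difference, which adds 0.5² = 0.25. The standard error ratio for the average treatment effect is √((0.5 + 2/28 + 0.25)/(0.5 + 2/28)) = √(0.821/0.571) = 1.20. The equivalent sample loss is 1 − 0.571/0.821 = 30%.

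**The case against.** **Independence carries Step 2.** With equal-probability items and pairwise within-day correlation ρ, φ at DDS mean 5 is 0.5 × (1 + 9ρ), which reaches 1 at ρ = 0.11. For SHDS at mean 7, φ is 0.5 × (1 + 13ρ), which reaches 1 at ρ = 0.08. Foods eaten together in mixed meals could produce that. This stands.

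**Partly recorded days add variance.** The Outcomes section foresees incomplete recalls. Suppose 30% of days capture half the groups, starting from mean 4.9 and variance 1.9. The mean becomes about 4.2 and the variance about 3.1, so φ is about 0.74 and the standard error ratio about 1.16. If those days scored zero, variance would exceed the mean. This also stands.

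**The missing detail may be elsewhere.** An analysis plan not shown may specify robust standard errors, and individual-level random effects do not exclude a random slope. That is fair as to standard errors and slopes. The distribution, however, is chosen in the article itself, and it is the part that cannot represent variance below the mean.

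**Low stakes.** DDS and SHDS are secondary outcomes of an unpowered pilot, and the primary outcomes involve no comparison of arms. What goes into sizing the next trial is the effect over four weeks, not the interaction p-value. This limits the weight of the point without removing it.

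**Country.** A country term is routine detail and may simply have been left out of a condensed account. A constant country difference is absorbed by the random intercept and barely touches the interaction.

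**Conclusion.** The concern holds in a two-directional form. The stated model ties within-person variance to the mean for bounded scores whose variance may well be smaller, and it names nothing that would protect the treatment-by-time standard error. That standard error is right only if φ happens to be near 1 or opposing errors cancel.

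With independent food groups and a common trend, it is 1.2–1.6 times (DDS) or 1.3–1.9 times (SHDS) too large, and 80% power becomes 38–68% or 19–58%. With differing trends and only a random intercept, type I error was 8–25% at the two larger slope SDs assumed.

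A reader might infer that the test loses about half its power. The documents do not support this. Halving 80% needs φ of about 0.4, and no mean, variance or effect is given: φ = 0.8 leaves 73%, while an SHDS mean of 10 leaves 19%. Nor do they support reading the test as always conservative, the rate ratio as biased, or the four-week average effect as compromised. The country point is secondary and concerns the precision of the average effect in the pooled analysis.

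**What to change.** Replace the Poisson specification for DDS and SHDS with a linear mixed model for the daily score, keeping treatment, day and their interaction, with a random intercept and a random day slope per participant. The slope is essential, since a random intercept alone does not control type I error when trends differ. Alternatively, keep the log link and report participant-clustered robust or bootstrap standard errors with a small-sample correction, as there are only 36 participants per country. Either route covers both directions of error.

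In the pooled analysis, include country as a fixed effect, because randomisation is done within country. The gain is mainly precision for the four-week treatment effect.

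The cost is a change of model wording and a few lines of code, with no new data. Under the linear model the effect is reported in score points rather than as a rate ratio; the second option keeps the ratio.
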